# SUBJECT SELECTION

## Study Population

Subjects with a diagnosis of IGT and IR who meet the inclusion and exclusion criteria will be eligible for participation in this study.

## Inclusion Criteria

1. Female 18-35 years of age at Visit outpatient.
2. Documentation of IGT/IR diagnosis as evidenced by one or more clinical features consistent with the IGT/IR phenotype and one or more of the following criteria:

- IGT：2-h PG in the 75-g OGTT 140 mg/dl (7.8mmol/l) to 199 mg/dl (11.0 mmol/l)
- M-value < 6.28 was considered to have IR

1. Written informed consent (and assent when applicable) obtained from subject or subject’s legal representative and ability for subject to comply with the requirements of the study.

## Exclusion Criteria

1. Pregnant, breastfeeding, or unwilling to practice birth control during participation in the study.
2. Presence of a condition or abnormality that in the opinion of the Investigator would compromise the safety of the patient or the quality of the data.
3. type 1 diabetes mellitus (T1DM), T2DM, hypertension, and other important organ diseases such as heart, liver, and kidney.
4. family history of thyroid tumor, the history of medullary thyroid carcinoma, severe gastrointestinal disease, acute pancreatitis

# Concurrent Medications

All subjects should be maintained on the same medications throughout the entire study period, as medically feasible, with no introduction of new chronic therapies.

## Allowed Medications and Treatments

Standard therapy for lira is allowed except for treatments noted in the exclusion criteria described above.Those subjects did not use any drugs in the last 3 months.

# STUDY TREATMENTS

## Method of Assigning Subjects to Treatment Groups

A total of 26 overweight / obese women with IR participated in GLP-1RA intervention for 24 weeks. Included age of 18-35 and BMI of 25-35 kg/m2.

## Formulation of Test Product

Lira is developed by Novo Nordisk, high doses (up to 3.0mg) of lira is for subcutaneously administration in the management of overweight/obese patients. Lira is a colorless or almost colorless clear isotonic liquid, pH=8.15.

## Supply of Study Drug at the Site

The designee will ship Lira to the investigational sites. The initial study drug shipment will be shipped after site activation (all required regulatory documentation has been received by the Sponsor and a contract has been executed). Subsequent study drug shipments will be made after site request for resupply.

### Dosage/Dosage Regimen

Liar was injected subcutaneously once a day. The dose increased from 0.6 mg to 1.8 mg. Inclusion criteria included age of 18-35 and BMI of 25-35 kg/m2.

### Dispensing

Lira was dispensed by pharmacist and Injected by investigator.

### Administration Instructions

Liar was injected subcutaneously once a day at the dose from 0.6 mg to 1.8 mg. The timing of the dose adjustment is determined by the investigator.

## Supply of Study Drug at the Site

The subjects were enrolled for intervention with lira due to ovarian dysfunction and refractory menstrual problems.All subjects signed informed consent before treatment. 26 subjects were followed up to the end of the study. Lira was supplied daily by the Pharmacy Department and delivered to the day clinic.

### Storage

Study drug should be stored by the study site in the refrigerator (2 to 8ºC) and and protected from light. If the temperature of study drug storage in the clinic/pharmacy exceeds or falls below this range, this should be reported to the Sponsor or designee and captured as a deviation.

## Study Drug Accountability

An accurate and current accounting of the dispensing and return of study drug for each subject will be maintained on an ongoing basis by a member of the study site staff. The number of study drug dispensed and returned by the subject will be recorded on the Investigational Drug Accountability Record. The study monitor will verify these documents throughout the course of the study.

## Measures of Treatment Compliance

Subjects will be asked to come to the study site and be injected lira at the same time every day. If they did not come, the designee would call to remind them to ensure their compliance.

# STUDY PROCEDURES AND GUIDELINES

A Schedule of Events representing the required testing procedures to be performed for the duration of the study is diagrammed in Appendix 1.

Prior to conducting any study-related activities, written informed consent and the Health Insurance Portability and Accountability Act (HIPAA) authorization must be signed and dated by the subject or subject’s legal representative. If appropriate, assent must also be obtained prior to conducting any study-related activities.

## Clinical Assessments

### Concomitant Medications

All concomitant medication and concurrent therapies will be documented at Baseline/Screening, 12 and 24 weeks after treatment. Dose, route, unit frequency of administration, and indication for administration and dates of medication will be captured.

### Demographics

Demographic information (date of birth, gender, race) will be recorded at Screening.

### Medical History

Relevant medical history, including history of current disease, other pertinent respiratory history, and information regarding underlying diseases will be recorded at Screening.

### Physical Examination

After fasting for 10-12 h, all subjects were given a physical examination and biochemical tests by professionals. The physical examination included body weight, blood pressure (BP), waist circumference (WC), and body fat content (Fat %). A complete physical examination will be performed by either the investigator or a subinvestigator who is a physician before treatment. Qualified staff (MD, NP, RN, and PA) may complete the abbreviated physical exam at all other visits. New abnormal physical exam findings must be documented and will be followed by a physician or other qualified staff at the next scheduled visit.

### Vital Signs

Physical examination and biochemical tests, OGTT, and EHC tests were performed before treatment, 12 and 24 weeks after treatment.

### Adverse Events

Information regarding occurrence of adverse events will be captured throughout the study. Duration (start and stop dates and times), severity/grade, outcome, treatment and relation to study drug will be recorded on the case report form.

## Clinical Laboratory Measurements

### Serum Fetuin-B concentration test

Serum Fetuin-B concentration was determined by an ELISA kit (RayBiotech, Inc. Norcross, GA, USA). The detection limit for Fetuin-B was 4.0 ng/ml. Intra- and inter-assay variations (CV) were 10 % and 12 %, respectively.

### Biochemical parameters

Blood will be obtained and sent to each site’s clinical chemistry lab for determination of total cholesterol (TC), triglyceride (TG), high-density lipoprotein cholesterol (HDL-C), low-density lipoprotein cholesterol (LDL-C), free fatty acid (FFA), HbA1c, FBG, 2-hour postprandial blood glucose (2h-BG), fasting insulin (FIns), and 2-hour postprandial insulin (2h- INS).

### OGTT Test

After 10-12 hours of fasting overnight, all subjects were given 75g glucose orally and the OGTT test was performed at 8:00 AM. During the OGTT, blood samples were collected for the measurements of blood glucose, insulin, and serum Fetuin-B at 0, 30, 60, and 120 min.

### EHC Test

The EHC was performed in all subjects. During the EHC, human insulin (1mU/kg/min) was continuously infused for 2 hours. At the same time, the infusion rate of the 20% glucose was adjusted according to the blood glucose levels, tested every 15 min, to maintain blood glucose at the basic level (4.5-5.5 mmol/L).

# EVALUATIONS BY VISIT

## Visit 1 (0 Week)

1. Review the study with the subject (subject’s legal representative) and obtain written informed consent and approved by the ethics committee of the Second Affiliated Hospital of Chongqing Medical University .
2. Assign the subject a unique screening number.
3. Record demographics data.
4. Record medical history,, and prior treatments.
5. Record concomitant medications.
6. Perform a complete physical examination.
7. Perform and record vital signs.
8. Perform and record results of blood pressure testing.
9. Collect blood for clinical laboratory tests (TC, TG, HDL-C, LDL-C, FFA, HbA1c, FBG, 2h-BG, FIns, 2h- INS).
10. Schedule subject for Visit 2 after 12 weeks.
11. List all additional procedures, such as Randomize subject, Dispense study drug, Initiate subject diary, etc.

## Visit 2 (12 weeks)

1. Record any Adverse Experiences and/or Review subject diary for adverse experiences and dosing compliance.
2. Concomitant medications review.
3. Perform abbreviated physical examination.
4. Perform and record vital signs.
5. Collect blood for clinical laboratory tests (TC, TG, HDL-C, LDL-C, FFA, HbA1c, FBG, 2h-BG, FIns, 2h- INS).
6. List all additional procedures.

## Visit 3 (24 weeks)

1. Record any Adverse Experiences and/or Review subject diary for adverse experiences and dosing compliance.
2. Record changes to concomitant medications.
3. Perform abbreviated physical examination.
4. Perform and record vital signs.
5. Collect blood for clinical laboratory tests (TC, TG, HDL-C, LDL-C, FFA, HbA1c, FBG, 2h-BG, FIns, 2h- INS).
6. List all additional procedures.

## Early Withdrawal Visit

1. Record any Adverse Experiences and/or Review subject diary for adverse experiences and exclusionary medication use.
2. Record changes to concomitant medications.
3. Perform complete physical examination.
4. Perform and record vital signs.
5. Collect blood for clinical laboratory tests (TC, TG, HDL-C, LDL-C, FFA, HbA1c, FBG, 2h-BG, FIns, 2h- INS).

# ADVERSE Experience REPORTING AND DOCUMENTATION

## Adverse Events

An adverse event (AE) is any untoward medical occurrence in a clinical investigation of a patient administered a pharmaceutical product and that does not necessarily have a causal relationship with the treatment. An AE is therefore any unfavorable and unintended sign (including an abnormal laboratory finding), symptom or disease temporally associated with the administration of an investigational product, whether or not related to that investigational product. An unexpected AE is one of a type not identified in nature, severity, or frequency in the current Investigator’s Brochure or of greater severity or frequency than expected based on the information in the Investigator’s Brochure.

The Investigator will probe, via discussion with the subject, for the occurrence of AEs during each subject visit and record the information in the site’s source documents. Adverse events will be recorded in the patient CRF. Adverse events will be described by duration (start and stop dates and times), severity, outcome, treatment and relation to study drug, or if unrelated, the cause.

**AE Severity**

The National Cancer Institute’s Common Terminology Criteria for Adverse Events (CTCAE) Version 3.0 should be used to assess and grade AE severity, including laboratory abnormalities judged to be clinically significant. The modified criteria can be found in the study manual. If the experience is not covered in the modified criteria, the guidelines shown in Table 1 below should be used to grade severity. It should be pointed out that the term “severe” is a measure of intensity and that a severe AE is not necessarily serious.

Table 1. AE Severity Grading

| **Severity (Toxicity Grade)** | **Description** |
| --- | --- |
| Mild (1) | Transient or mild discomfort; no limitation in activity; no medical intervention or therapy required. The subject may be aware of the sign or symptom but tolerates it reasonably well. |
| Moderate (2) | Mild to moderate limitation in activity, no or minimal medical intervention/therapy required. |
| Severe (3) | Marked limitation in activity, medical intervention/therapy required, hospitalizations possible. |
| Life-threatening (4) | The subject is at risk of death due to the adverse experience as it occurred. This does not refer to an experience that hypothetically might have caused death if it were more severe. |

**AE Relationship to Study Drug**

The relationship of an AE to the study drug should be assessed using the following the guidelines in Table 2.

Table 2. AE Relationship to Study Drug

| **Relationship to Drug** | **Comment** |
| --- | --- |
| Definitely | Previously known toxicity of agent; or an event that follows a reasonable temporal sequence from administration of the drug; that follows a known or expected response pattern to the suspected drug; that is confirmed by stopping or reducing the dosage of the drug; and that is not explained by any other reasonable hypothesis. |
| Probably | An event that follows a reasonable temporal sequence from administration of the drug; that follows a known or expected response pattern to the suspected drug; that is confirmed by stopping or reducing the dosage of the drug; and that is unlikely to be explained by the known characteristics of the subject’s clinical state or by other interventions. |
| Possibly | An event that follows a reasonable temporal sequence from administration of the drug; that follows a known or expected response pattern to that suspected drug; but that could readily have been produced by a number of other factors. |
| Unrelated | An event that can be determined with certainty to have no relationship to the study drug. |

## Serious Adverse Experiences (SAE)

An SAE is defined as any AE occurring at any dose that results in any of the following outcomes:

- death
- a life-threatening adverse experience
- inpatient hospitalization or prolongation of existing hospitalization
- a persistent or significant disability/incapacity
- a congenital anomaly/birth defect

Other important medical events may also be considered an SAE when, based on appropriate medical judgment, they jeopardize the subject or require intervention to prevent one of the outcomes listed.

### Serious Adverse Experience Reporting

Study sites will document all SAEs that occur (whether or not related to study drug) per [UCSF CHR Guidelines](http://www.research.ucsf.edu/chr/Guide/Adverse_Events_Guidelines.asp" \l "2). The collection period for all SAEs will begin after informed consent is obtained and end after procedures for the final study visit have been completed.

In accordance with the standard operating procedures and policies of the local Institutional Review Board (IRB)/Independent Ethics Committee (IEC), the site investigator will report SAEs to the IRB/IEC.

# DISCONTINUATION And Replacement of subjects

## Early Discontinuation of Study Drug

A subject may be discontinued from study treatment at any time if the subject, the investigator, or the Sponsor feels that it is not in the subject’s best interest to continue. The following is a list of possible reasons for study treatment discontinuation:

- Subject withdrawal of consent (or assent)
- Subject is not compliant with study procedures
- Adverse event that in the opinion of the investigator would be in the best interest of the subject to discontinue study treatment
- Protocol violation requiring discontinuation of study treatment
- Lost to follow-up
- Sponsor request for early termination of study
- Positive pregnancy test (females)

If a subject is withdrawn from treatment due to an adverse event, the subject will be followed and treated by the Investigator until the abnormal parameter or symptom has resolved or stabilized.

All subjects who discontinue study treatment should come in for an early discontinuation visit as soon as possible and then should be encouraged to complete all remaining scheduled visits and procedures.

All subjects are free to withdraw from participation at any time, for any reason, specified or unspecified, and without prejudice.

Reasonable attempts will be made by the investigator to provide a reason for subject withdrawals. The reason for the subject’s withdrawal from the study will be specified in the subject’s source documents Refer to Section 10 for early termination procedures.

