APPENDIX 1. Schedule of Study Visits

|  | **Visit 1 (Day/Week/Month #)a** | **Visit 2 (Day/Week/Month #)a** | **Visit 3 (Day/Week/Month #)a** |
| --- | --- | --- | --- |
| Informed Consent | **x** |  |  |
| Medical History | **x** |  |  |
| Complete Physical Exam | **x** |  |  |
| Abbreviated Physical Exam |  | **x** | **x** |
| Height | **x** | **X** | **X** |
| Weight | **x** | **x** | **x** |
| WC |  |  |  |
| FAT% |  |  |  |
| Vital Signs | **x** | **x** | **x** |
| Pharmacokinetics |  | **x** |  |
| Serum Fetuin-B | **x** |  |  |
| Pregnancy Test (Urine or Serum) | **x** |  |  |
| Hematology | **x** |  |  |
| OGTT | **x** |  |  |
| EHC | **x** |  |  |
| Urinalysis | **x** |  |  |
| Dispensing or Administration of Study Drug | **X** | **X** | **X** |
| Counting of Returned Study Drug |  | **X** | **X** |
| Concomitant Medication Review | **X** | **X** | **X** |
| Adverse Experiences |  |  |  |

a 2 days

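### A positive pregnancy test is a listed reason to stop liraglutide, but no pregnancy test is planned after Visit 1 in 24 weeks of treatment

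*Protocol*

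**What the plan says.** Four parts of the protocol bear on pregnancy during treatment.

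- **Entry.** The Exclusion Criteria rule out women who are "Pregnant, breastfeeding, or unwilling to practice birth control during participation in the study". The synopsis also names pregnancy among the liraglutide-specific exclusions.
- **Stopping.** The section Early Discontinuation of Study Drug gives a list of possible reasons to stop, which includes "Positive pregnancy test (females".
- **Schedule.** Study Procedures and Guidelines states: "A Schedule of Events representing the required testing procedures to be performed for the duration of the study is diagrammed in Appendix 1". In Appendix 1 the row "Pregnancy Test (Urine or Serum" is marked at Visit 1; its cells for Visits 2 and 3 are empty.
- **Visit lists.** At Visit 2 the laboratory item reads "Collect blood for clinical laboratory tests (TC, TG, HDL-C, LDL-C, FFA, HbA1c, FBG, 2h-BG, FIns, 2h- INS". Visit 3 and the early withdrawal visit carry the same metabolic panel. The early withdrawal list opens with "Record any Adverse Experiences and/or Review subject diary for adverse experiences and exclusionary medication use". None of the three names a pregnancy test.

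The treated women are aged 18 to 35. The second section headed Supply of Study Drug at the Site says they were given liraglutide because of disordered ovarian function and menstrual problems that had not responded to treatment.

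**The concern.** The protocol treats pregnancy as a bar to starting liraglutide and as a possible reason to stop it, and it asks for birth control throughout participation. It then plans no means of finding a pregnancy once dosing has begun. The Visit 1 test serves the entry criterion and cannot serve the stopping reason.

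What is at stake is participant safety. Followed as written, an unsuspected pregnancy could continue under daily injections at up to 1.8 mg. The woman could also undergo the week 12 and week 24 clamps, each a two-hour insulin infusion, without a planned check. The protocol counts a congenital anomaly as a serious adverse event, yet no end-of-treatment test would identify an exposed pregnancy to follow up. In women treated for menstrual disturbance, a missed period may also be a weaker prompt for an unscheduled test than usual.

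**Working it through.** The check is mainly a cross-reading of the schedule, with a little arithmetic on its size.

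**1. Planned pregnancy tests, by visit**

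| Visit | Appendix 1 | Visit list in the body |
| --- | --- | --- |
| Visit 1 (week 0) | marked | not named |
| Visit 2 (week 12) | blank | not named |
| Visit 3 (week 24) | blank | not named |
| Early withdrawal | no column | not named |

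The section Clinical Laboratory Measurements covers Fetuin-B, biochemistry, OGTT and clamp, and adds no pregnancy test. Planned tests after treatment starts: 0. The baseline test itself rests on Appendix 1 alone.

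**2. Could the blank cells be a slip that other text corrects?** Appendix 1 is visibly incomplete. It also marks OGTT and EHC at Visit 1 only. For those, however, the section Vital Signs supplies the later assessments: "Physical examination and biochemical tests, OGTT, and EHC tests were performed before treatment, 12 and 24 weeks after treatment". The Secondary Objectives do the same. No corresponding sentence was found for a pregnancy test. The line at Visits 2 and 3 asking for further procedures to be listed is an unfilled template item and schedules nothing.

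**3. Size**

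Inputs: 24 weeks of treatment (Primary Efficacy Endpoint); Visit 2 at 12 weeks; 26 treated women (Method of Assigning Subjects to Treatment Groups); 30 planned (Interim Analysis). Days are nominal and ignore the two-day visit window in Appendix 1.

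- Treatment length: 24 × 7 = 168 days.
- Longest untested interval on drug as planned: 168 days.
- Day of Visit 2: 12 × 7 = 84.
- Longest untested interval with a Visit 2 test: max(84, 168 − 84) = 84 days.
- Tests for Visit 2 alone: 26 × 1 = 26 to 30 × 1 = 30.
- Tests for Visit 2 plus one end-of-treatment test per woman: 26 × 2 = 52 to 30 × 2 = 60.

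Among the numbered visits after baseline, Visit 2 is the only one at which a positive result could still stop treatment, because Visit 3 falls at its end.

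**The case against.** The strongest reply is that nothing here is contradictory. The list gives possible reasons, not mandatory rules. Other items on it, such as loss to follow-up or withdrawal of consent, have no scheduled assessment either. The investigator may stop treatment at any time, so a test done for cause satisfies the list. This is correct as far as it goes, and the point is therefore one of design rather than contradiction. But loss to follow-up and withdrawal of consent make themselves known, whereas an early pregnancy may not.

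A second reply is that Appendix 1 is a half-filled template, with several rows empty altogether, so its blanks say little about intent. That is fair about the table. It does not help here, because the body text fills the OGTT, EHC and adverse-event rows and leaves this one unfilled. The contents list also names safety-reporting and monitoring sections (11.3 to 11.5) whose text was not available for checking. Their titles do not suggest a test schedule, but the statement that no later test is planned is limited to the text that could be read.

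A third reply is that the risk is already low. Birth control is required, and daily contact is planned: "Subjects will be asked to come to the study site and be injected lira at the same time every day". Both lower the risk, and daily attendance offers many occasions for an unscheduled test. Neither is a test. That a missed period would go unremarked in these women is plausible but remains conjecture.

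Finally, the protocol says in the past tense that 26 women were followed to the end, so an amendment may come too late for them. Other sections are written prospectively, and the mixed tense does not supply the missing test.

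**Conclusion.** The concern holds. In the text that could be checked, one pregnancy test is planned, at week 0, and none during or at the end of 168 days of daily liraglutide in women aged 18 to 35. The listed stopping reason therefore depends wholly on an unscheduled test or on self-report.

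The size is modest: 26 treated women (30 planned), with partial safeguards in place and no effect on the primary objective, sample size, power or alpha. It is a participant-safety gap that should be closed because closing it is cheap. The conclusion assumes that Appendix 1 and the visit lists are followed as written and that the sections not available for checking do not schedule a test.

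**What to change.** - In Appendix 1 and the Visit 2 list, add a urine or serum pregnancy test at week 12, on the blood already drawn if preferred.
- In Appendix 1, the Visit 3 list and the early withdrawal list, add an end-of-treatment test. It cannot stop dosing, but it identifies an exposed pregnancy.
- Name the Visit 1 test in the Visit 1 list so that it agrees with Appendix 1; this is clerical.
- Leave any more frequent testing during daily attendance to the investigator and the ethics committee. A week 12 test alone still leaves up to 84 days between tests.

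The cost is a short amendment and one or two inexpensive tests per treated woman: 26 to 30 tests for Visit 2 alone, 52 to 60 with the end-of-treatment test. No extra visit or blood draw is needed, since blood is already taken at Visits 2 and 3 and at early withdrawal.
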